### **STUDY OUTCOME**

- Estimates for the screening performance of ED trigger criterion for an early ECG to identify STEMI including sensitivity, specificity, NPV, PPV, LR+, LR-, and the missed case rate (false negative rate)
- Description of whether the comprehensiveness of the criteria influences screening performance.

## SIGNIFICANCE

This will be the first study to evaluate ED STEMI trigger criteria screening performance across institutions in different regions of the United States.

## PERFORMANCE OF STEMI SCREENING TRIGGER CRITERIA

Online form available at: <https://redcap.vanderbilt.edu/surveys/?s=ET3WK99HDM>

---

The electrocardiogram (ECG) is often described as a screening test for ST-elevation myocardial infarction (STEMI), with coronary angiography as the criterion standard diagnostic test. However, in the emergency department (ED), treatment is initiated based on the presence of STEMI on ECG. In addition, timely diagnosis should be made within 10 minutes, well before a patient is seen by a physician and during the processes of registration and triage. As a result, in the context of ED patient care processes and flow, the ECG is the **diagnostic test** and the clinical criteria used to screen arriving ED patients for STEMI in during registration and triage (ECG trigger criteria) is the true **screening test**.

This study seeks to quantify the screening performance of the early ECG trigger criteria used to screen for STEMI across 7 geographically diverse EDs. The screening population includes all ED patients  $\geq 18$  years of age seen in the ED from January 1, 2014 at 12:00am to December 31, 2014 at 11:59am. It assumes that all ECGs done within the first 15 minutes of an ED visit are to screen for STEMI. The **STEMI screening criteria** is the index test. Triggering an early ECG is a positive index test. An **early ECG** (performed  $\leq 15$  minutes after patient arrival) is the reference diagnostic test standard. An ECG demonstrating STEMI is a positive reference test. Patients, who do not receive an early ECG from registration or triage, go on to receive typical ED care. This provides an opportunity to identify cases missed by the index test, making typical ED care an alternative reference standard for trigger negative patients.

### Key Definitions

Trigger positive = early ECG to screen for STEMI = an ECG performed  $\leq 15$  minutes of arrival

Arrival = first documented presence or time-stamp of the patients presence in the ED

EMS = patients coming to the ED via emergency medical system (EMS) ambulance or helicopter

Walk-in = patients coming to the ED via non-EMS transportation

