### Rationale

The ECG is often referred to as the screening test for STEMI. This is because 30-50% of patients with STEMI on ECG will not have an occlusive coronary artery thrombus when evaluated with coronary artery angiography, the criterion (gold) standard diagnostic test. Despite this limitation, the risk-benefit balance of early treatment verses further testing weighs in favor of early treatment. As a result, treatment is initiated based on the *reference diagnostic testing standard*, an ECG demonstrating STEMI. In the context of ED operations and patient flow, the trigger criteria is the

true screening test. Patients, who do not receive an early ECG from registration or triage, go on to receive typical ED care. This provides an opportunity to identify cases missed by the index test, making typical ED care an *alternative reference standard* for trigger negative patients.

We have looked at the STEMI screening performance at Vanderbilt University (Table S1). In doing so we considered a patient meeting trigger criteria, which prompts the ED registration or triage staff to initiate an early ECG, as a positive *index test*, and an ECG indicating STEMI as a positive *reference test*. We found that the screening process has high sensitivity and negative predictive value with poor positive predictive value and limited specificity. The likelihood ratio of positive test is 5.2 (probability of a person with a STEMI ECG screening positive via screening trigger criteria), and that of a negative test is 0.025 (probability of a person with a STEMI ECG not being identified with screening trigger criteria). This study seeks to understand these local results in the context of broader clinical practice and variability of trigger criteria between institutions.

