#### **Data Collection**

A site-PI from each ED will be responsible for extracting aggregate figures included in the study survey (Appendix I) using data from their EMR reporting functions and their hospital STEMI case review committee. To reduce misclassification bias, STEMI is defined using ICD-9 codes previously validated in the literature (410.01, 410.11, 410.21, 410.31, 410.41, 410.51, 410.61, 410.81, 410.91). The EMR will provide aggregated numbers on ED care events (number of patients seen, number of patients receiving an early ECG as a result of triggering the screening criteria, etc.), while the hospital STEMI committee report will provide verifying counts for all ED STEMI cases, whether the early ECG demonstrated STEMI, and missed ED STEMI cases. For any discrepancies between the EMR and STEMI committee reports, the site PI will review the associated patient charts and make a clinical decision on whether the case was Trigger positive or negative, and STEMI positive or negative. The survey is included as appendix I, and will be sent to the site-PIs via email using REDCap. REDCap will also serve as a secure study data repository. The questionnaire has been reviewed by a biostatistician for completeness and to ensure it appropriately supports the planned analysis. (see attached)

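### A positive index test is defined both as meeting the trigger criteria and as an ECG within 15 minutes; only the second is measured, so the results describe the screening process and not the criteria alone

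*Protocol*

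**What the plan says.** The Rationale describes the lead-site work in terms of the criteria: "we considered a patient meeting trigger criteria, which prompts the ED registration or triage staff to initiate an early ECG, as a positive" index test. The survey preamble (Performance of STEMI Screening Trigger Criteria) also names the criteria as the index test, but gives the positive result as an event: "Triggering an early ECG is a positive index test". It adds a working assumption: "It assumes that all ECGs done within the first 15 minutes of an ED visit are to screen for STEMI".

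Key Definitions uses the clock alone: "Trigger positive = early ECG to screen for STEMI = an ECG performed" no later than 15 minutes after arrival. Data Collection describes the EMR count in words that require both conditions: "number of patients receiving an early ECG as a result of triggering the screening criteria".

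Survey question 7 asks for all adults with an ECG within 15 minutes. Question 9 asks for STEMI cases without one and labels them as missed by screening. Table S2 builds every cell from questions 6 to 9. No survey item asks whether any patient met the criteria.

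Where the EMR and the STEMI committee report disagree, Data Collection has the site PI review the charts and "make a clinical decision on whether the case was Trigger positive or negative, and STEMI positive or negative".

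**The concern.** Meeting the criteria and having an ECG within 15 minutes are different facts about a patient. They part in two ways. A patient may meet the criteria and get the ECG at minute 20, because of crowding or staffing. Or a patient may get an ECG at minute 8 for a reason outside the written criteria.

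This matters most for Objective 2, which relates likelihood ratios to what the criteria contain. ECG delay is not a property of criteria content. With seven EDs as the units, one slow ED with comprehensive criteria could weaken or distort the association, and the four counts in Table S2 would not reveal why.

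The adjudication step raises a second problem. If trigger status follows from an arrival time and an ECG time, there is nothing clinical to decide. Yet one person, at the ED being assessed and with the whole chart in view, decides both axes of the table for discrepant cases. No rule, order or blinding is given. The false-negative cell, where such decisions may fall, is the smallest in the table.

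**Working it through.** **Inputs.** Table S1 (lead site): 60 true positives, 13,092 false positives, 15 false negatives, 55,454 true negatives; 75 STEMI, 68,546 non-STEMI, 68,621 in all. I read these as counts under the 15-minute rule, which is how the survey will count them. The Rationale describes the same table in terms of meeting criteria, so this reading is an assumption.

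**Reproducing the plan's figures.**
- Sensitivity = 60/75 = 80.0% (stated 80%).
- Specificity = 55,454/68,546 = 80.9% (stated 81%).
- LR+ = 0.800/(1 − 0.809) = 4.19.
- LR- = (1 − 0.800)/0.809 = 0.247.
- Table S2 with #6 = 68,621, #7 = 13,152, #8 = 75, #9 = 15 gives #8 − #9 = 60; #7 − #8 + #9 = 13,092; #9 = 15; #6 − #7 − #9 = 55,454. These are the Table S1 cells.

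**What the criteria themselves would score.** Let
- k = false negatives who met the criteria but had no ECG within 15 minutes;
- j = true positives who had an early ECG without meeting the criteria;
- m = non-STEMI patients who met the criteria but had no early ECG;
- n = non-STEMI patients with an early ECG who did not meet the criteria.

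Then criteria sensitivity = (60 + k − j)/75 and criteria specificity = (55,454 − m + n)/68,546. The protocol gives none of k, j, m or n, and the survey collects none. The rows below are illustrations with assumed values; quantities not named are zero.

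| Assumed | Sensitivity | Specificity | LR+ | LR- |
|---|---|---|---|---|
| none (as planned) | 60/75 = 80.0% | 80.9% | 4.19 | 0.247 |
| k = 5 | 65/75 = 86.7% | 80.9% | 4.54 | 0.165 |
| k = 10 | 70/75 = 93.3% | 80.9% | 4.89 | 0.082 |
| k = 10, m = 2,618 | 93.3% | 52,836/68,546 = 77.1% | 4.07 | 0.086 |
| j = 6 | 54/75 = 72.0% | 80.9% | 0.720/0.191 = 3.77 | 0.280/0.809 = 0.346 |

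Here m = 2,618 is 20% of the 13,092 false positives. Three things follow. Sensitivity can move either way. Correcting only the STEMI column at k = 10 raises LR+ from 4.19 to 4.89, but moving non-STEMI patients as well brings it to 4.07, below the planned value. And at an ED with no written criteria, which questions 3 and 5 allow, all four quantities are undefined.

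**Adjudication.** Under Key Definitions, trigger status is a function of two time stamps. Under Data Collection, it is a clinical judgement in discrepant cases. Both cannot hold for the same patient.

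**The case against.** The best defence is that the time stamp is a declared proxy. The Rationale ties meeting the criteria to prompting an early ECG, and it speaks of a screening process. The preamble stresses timely diagnosis and states its assumption about early ECGs. For Objective 1, counting a late ECG as a failed screen is a reasonable process-level choice. That stands. It does not rescue Objective 2: the assumption covers early ECGs only and is silent on patients who met the criteria and were tested late.

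Questions 16 to 24 collect door-to-ECG quartiles, separately for STEMI patients tested after 15 minutes, so a slow ED is not invisible. That also stands, although the quartiles do not show who met the criteria.

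A reader might infer more than the text supports:
- *That the site PI's decision is a third definition.* It applies only where the two sources disagree. It is an adjudication step without a rule.
- *That five reclassified cases bound its effect.* The expectation of at most five reviews stands in question 8 and concerns the STEMI count, not trigger status.
- *That the criteria's true sensitivity is higher than 80%.* This needs an assumed k with j = 0, and the protocol supports neither.
- *That the Rationale's likelihood ratios (5.2 and 0.025), which do not match the 4.19 and 0.247 from Table S1, result from the two definitions.* The protocol does not say how they were obtained; this is a separate inconsistency.
- *That splitting #9 by whether criteria were met would repair the likelihood ratios.* It would join a criteria-based sensitivity to a time-based specificity, could only raise sensitivity, cannot be applied where no criteria exist, and would add chart review by assessors who know the cases are missed STEMIs.

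**Conclusion.** The point holds in limited form. There are two definitions of a positive index test, and only the 15-minute rule reaches the data. The Table S2 estimates are valid as measures of the screening process under that rule, but not as measures of the criteria. Objective 2 can show an association between criteria content and process performance; it cannot separate content from ECG speed. Neither the size nor the direction of the difference can be derived from the protocol, and the illustrations above rest wholly on assumed counts.

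The conflict over trigger status in discrepant cases is a plain contradiction between Data Collection and Key Definitions. Its numerical effect is also unknown, but it can be removed by a change of wording.

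**What to change.** 1. Use the Key Definitions rule throughout. In Data Collection, delete the clinical decision on trigger status, so that it is set by the arrival and ECG time stamps alone.
2. For discrepant cases, have the site PI decide and record STEMI status before the ECG time is looked up.
3. Reword the Rationale, Study Objectives, Study Outcome and survey preamble so that the estimates are of screening-process performance (ECG within 15 minutes of arrival). Limit the Objective 2 conclusion to an association of criteria content with process performance, and read it alongside the door-to-ECG times from questions 16 to 24.
4. Optionally, EDs with written criteria may report how many #9 cases met them. Keep this as a descriptive count and do not form likelihood ratios from it.

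Items 1 to 3 need no new data and no additional chart review; item 2 only fixes the order within reviews already planned. The price is scientific: the study can say less about the criteria themselves. Item 4, if taken up, costs a chart look-up of the #9 cases at those EDs.

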### Data Collection Sources

ED and hospital electronic medical record, or summative case counts from a hospital STEMI Case Review Committee

---

## SURVEY

1) ED Name: [drop down menu]

- Select one
- Brigham and Women's Hospital
- Hospital of the University of Pennsylvania
- Vanderbilt University
- University of Wisconsin
- University of Texas Southwestern
- Oregon Health & Sciences University
- University of California - Davis

2) Please upload a copy of your IRB approval letter as a pdf file.

3) In 2014, how did you identify arriving ED patients for an early ECG to screen for STEMI?

[drop down menu]

- Select one
- Established registration/triage criteria or protocol
- Solely at the discretion of the registration staff or triaging provider

*\*EDOSG Baseline Data Collection Tool Question #41*

4) If you have an established early ECG protocol that serve as your “trigger criteria,” upload a PDF or MS Word document including the criteria/policy for which patients get an early ECG to screen for STEMI.

5) In addition to “chest pain” what elements are included in your early ECG screening trigger criteria to identify patients for an early ECG? Select all that apply:

- Atypical STEMI symptoms (shortness of breath, dyspnea on exertion, fatigue, nausea)
- Associated STEMI symptoms (arm pain, jaw pain, back pain, epigastric pain, abdominal pain)
- An age threshold
- Other
- Not applicable. We do not have an established trigger criteria

6) What was the total number of patients,  $\geq 18$  years of age, seen in the ED in 2014? Include all individuals registered as ED patients. Do not exclude the following ED dispositions: eloped, left without being seen, left before completing treatment, left AMA.

<<Free text response>>

7) In 2014, what was the total number of patients ( $\geq 18$  years of age) that had an ECG performed  $\leq 15$  minutes after their arrival in the ED?

<<Free text response>>

8) What was the total number of 2014 STEMI cases that came through the ED? Include all patients,  $\geq 18$  years of age, who were registered as ED patients? This is either all ED patients with an ED admission or hospital discharge diagnosis of STEMI (via an electronic medical record query for diagnosis “STEMI” or ICD9 codes 410.01, 410.11, 410.21, 410.31, 410.41, 410.51, 410.61, 410.81, 410.91). Confirm this number with your hospital STEMI Case Review Committee. If there is a discrepancy, review the individual patient charts. Based on Vanderbilt data, the incidence of STEMI reported in the literature, and all participant ED patient volumes, there should be no more than 5 cases that require review.

<<Free text response>>

9) What was the total number of 2014 STEMI cases that came through the ED that did not get an early ECG (ECG  $\leq 15$  minutes of arrival)? These are the missed screening cases. This can be obtained as an adjudicated case count from your hospital STEMI committee. Many STEMI quality improvement committees will document time-to-ECG permitting an assessment of those missed by screening. These should not include patients whose were screened, but had STEMI-negative early ECGs.

<<Free text response>>

10) What was the total number of 2014 ED patients who had both an ECG performed and a serum troponin ordered and resulted. This is an estimate of the underlying “chest pain patient” burden.

<<Free text response>>

|                                                                                                                                                                                                                                                                      | Greeter               | Check-in Kiosk        | Registration Clerk    | Triage RN             | Midlevel Provider     | Physician             | Other                 |
|----------------------------------------------------------------------------------------------------------------------------------------------------------------------------------------------------------------------------------------------------------------------|-----------------------|-----------------------|-----------------------|-----------------------|-----------------------|-----------------------|-----------------------|
| 11) Who/what is the first contact for ED patient brought in by EMS? (select one)                                                                                                                                                                                     |  |  |  |  |  |  |  |
| 12) Who/what records EMS arrival patients' presenting chief complaint? (select one)                                                                                                                                                                                  |  |  |  |  |  |  |  |
| 13) Who/what is the first contact for arriving ED patients what walk-in? (select one)                                                                                                                                                                                |  |  |  |  |  |  |  |
| 14) Who/what records walk-in patients' presenting chief complaint? (select one)                                                                                                                                                                                      |  |  |  |  |  |  |  |
| 15) How many hours did it take to collect the data? Please include all time spent meeting, generating reports, extracting and cleaning data by you or your proxy (IT staff or assistant). Exclude time preparing your IRB application. Round up to the nearest hour. |                       |                       |                       |                       |                       |                       |                       |
| 16) What is the median Door- to-ECG time for all primarily screened ED patients with a final hospital diagnosis of STEMI?                                                                                                                                            |                       |                       |                       |                       |                       |                       |                       |
| 17) What is the 25th percentile Door-to-ECG time for all primarily screened ED patients with a final hospital diagnosis of STEMI?                                                                                                                                    |                       |                       |                       |                       |                       |                       |                       |
| 18) What is the 75th percentile Door-to-ECG time for all primarily screened ED patients with a final hospital diagnosis of STEMI?                                                                                                                                    |                       |                       |                       |                       |                       |                       |                       |
| 19) What is the median Door- to-ECG time for all primarily screened ED patients with a final hospital diagnosis of STEMI, who received their ECG $\leq 15$ minutes of ED arrival?                                                                                    |                       |                       |                       |                       |                       |                       |                       |
| 20) What is the 25th percentile Door-to-ECG time for all primarily screened ED patients with a final hospital diagnosis of STEMI, who received their ECG $\leq 15$ minutes of ED arrival?                                                                            |                       |                       |                       |                       |                       |                       |                       |
| 21) What is the 75th percentile Door-to-ECG time for all primarily screened ED patients with a final hospital diagnosis of STEMI, who received their ECG $\leq 15$ minutes of ED arrival?                                                                            |                       |                       |                       |                       |                       |                       |                       |
| 22) What is the median Door- to-ECG time for all primarily screened ED patients with a final hospital diagnosis of STEMI, who received their ECG $> 15$ minutes of ED arrival?                                                                                       |                       |                       |                       |                       |                       |                       |                       |
| 23) What is the 25th percentile Door-to-ECG time for all primarily screened ED patients with a final hospital diagnosis of STEMI, who received their ECG $> 15$ minutes of ED arrival?                                                                               |                       |                       |                       |                       |                       |                       |                       |
| 24) What is the 75th percentile Door-to-ECG time for all primarily screened ED patients with a final hospital diagnosis of STEMI, who received their ECG $> 15$ minutes of ED arrival?                                                                               |                       |                       |                       |                       |                       |                       |                       |
| 25) What was your hospital Case Mix Index (CMI) for 2014?                                                                                                                                                                                                            |                       |                       |                       |                       |                       |                       |                       |

**Table S1:** Early ECG Trigger Criteria Screening Performance

| [figure not shown]
Vanderbilt University
Medical Center |               | Truth                                   |                                            |                 |
|------------------------------------------------------------------------------------------------------------------------------|---------------|-----------------------------------------|--------------------------------------------|-----------------|
|                                                                                                                              |               | STEMI                                   |                                            |                 |
|                                                                                                                              |               | (+)
null false                       | (-)
null true                           |                 |
| Test
(Screening
Criteria)                                                                                              | Screen
(+) | 60
true positive                     | 13,092
false positive
(Type I Error) | 13,152          |
|                                                                                                                              | Screen
(-) | 15
false negative
(Type II Error) | 55,454
true negative                    | 55,469          |
|                                                                                                                              |               | 75                                      | 68,546                                     | 68,621          |
|                                                                                                                              |               | Sensitivity (1-β)
80%                | Specificity
81%                         | Accuracy
81% |

**Table S2:** 2x2 Contingency Table Data (Question numbers included below)

|                                          |             | Disease
ECG = Reference Test |           |       |
|------------------------------------------|-------------|---------------------------------|-----------|-------|
|                                          |             | STEMI (+)                       | STEMI (-) |       |
| Test
Trigger Criteria
= Index Test | Trigger (+) | #8-#9                           | #7-#8+9   | #7    |
|                                          | Trigger (-) | #9                              | #6-#7-#9  | #6-#7 |
|                                          |             | #8                              | #6-#8     | #6    |

